### Multifaceted implementation strategy

Intervention departments will receive the multifaceted implementation strategy of the PA, which incorporates three components. After baseline measurement (month 1), a working group (month 2), supervisor training (month 3) and supervisor coaching (months 4–12) will be carried out.

#### First component: working group

A two-hour working group meeting, chaired by an in-company OHP, will be organised before, and nine months after, supervisor training. The working group consists of a maximum ten representatives of managers, supervisors, employees, HR professionals, and OHPs. In the first meeting, baseline results will be presented to elaborate on signals of reduced work functioning, situations in which supervisors should apply PA, and barriers to and facilitators for implementation of PA. Working group results will be summarised in a manual for supervisor training and coaching. In a follow-up meeting, the working group will be asked to evaluate barriers and facilitators for implementation of PA.

#### Second component: supervisor training

Supervisors will be trained in applying PA by in-company OHPs in a four-hour session and an optional follow-up meeting of two hours. Before supervisor training, in-company OHPs are trained by the research team ([name], [name], [name], [name]) and provided with a training manual. For this study, application of PA is adjusted for the prevention of sick leave and worded in a workplace intervention protocol for supervisors. This protocol consists of seven steps to identify and solve employees’ work functioning problems due to health complaints (see Table 1). The protocol incorporates three supervisor-employee meetings with the supervisor both as participant and process leader. In the first meeting the employee is informed by the supervisor about the protocol and about both their roles in the next meetings. If needed, an employee may ask for an in-company OHP to act as a neutral process leader when applying this protocol.

**Table 1 T1:** Workplace intervention protocol for supervisors

**Meeting 1**	Step 1. Supervisor addresses employee’s reduced work functioning due to health complaints or being at risk for sick leave. Supervisor informs employee about the workplace intervention protocol of the study.
**Preparation**	Step 2. Employee makes an inventory of work tasks and activities, and prioritises work functioning problems within activities. Employee thinks of possible solutions for the two most important work functioning problems.
	Step 3. Supervisor makes an inventory of work tasks and activities for the employee, and prioritises work functioning problems within activities. Supervisor thinks of possible solutions for the two most important work functioning problems.
**Meeting 2**	Step 4. Supervisor and employee discuss work functioning problems and associated solutions, and assess the applicability of these solutions.
	Step 5. Supervisor and employee agree on action plan to realise solutions. If they don’t agree, supervisor asks in-company occupational health professional to act as process leader.
**Realisation**	Step 6. Solutions are prepared and realised.
**Meeting 3**	Step 7. Supervisor and employee evaluate action plan and realised solutions.

#### Third component: supervisor coaching

As a follow-up of the training, supervisors will be coached by an in-company OHP during the application of PA, if they want to. For example, a supervisor can prepare an up-coming meeting with an employee together with the in-company OHP. In addition, if supervisors find it difficult to be a participant as well as a process leader, they can ask an in-company OHP to act as process leader.

### Minimal implementation strategy

Control departments and their supervisors and employees will receive the minimal implementation strategy, consisting of distribution of written information about PA.

### Use of co-interventions

During this study, department managers and supervisors will be regularly asked about ongoing or planned reorganisations and in-company projects, which may influence results of this study.

### Outcome measures

#### Primary outcome measure

The primary outcome measure is self-efficacy of supervisors in joint problem solving to improve work functioning of employees with health complaints, and to prevent sick leave. Three items of the competence scale of the Empowerment questionnaire of Spreitzer et al. are modified to the context of this study [20]. For example, ‘I am confident about my ability to find and realise solutions together with my employee’. In accordance with the scale of Spreitzer et al. a seven-point Likert scale is used, ranging from 1 (totally disagree) to 7 (totally agree) [20].

#### Secondary outcome measures

Secondary outcomes will be measured both at supervisor and employee level.

#### Supervisors

Self-efficacy in communicating with employees about situations of reduced work functioning or being at risk for sick leave will be measured with 3 self-formulated items; for example, ‘I am self assured about addressing these situations together with my employee’. Also supervisors’ attitude, social influence and intention to address situations of reduced work functioning or being at risk for sick leave will be measured with self-formulated items. Three items are used to assess attitude; for example, ‘to address and solve these situations is important for me’. Two items are used to assess social influence; for example, ‘employees expect me to find and realise solutions together’. And one item is used to assess intention; for example, ‘it is very likely that my employee and I would find and realise solutions together’. Response categories for all items range from 1 (totally disagree) to 5 (totally agree).

#### Employees

Employees’ attitude, self-efficacy, and social influence about addressing situations of reduced work functioning or being at risk for sick leave will be measured by self-formulated items. Three items are used to assess attitude; for example, ‘in these situations it is important to inform your supervisor in time’. Three items will be used to assess self-efficacy; for example, ‘I have mastered the skills to address these situations with my supervisor’. Social influence will also be measured with three items; for example, ‘my organisation stimulates me to address these situations with my supervisor’. Response categories for all items range from 1 (totally disagree) to 5 (totally agree). Work functioning will be measured with ten items of a Dutch questionnaire about health and work [21]; for example, ‘I was at work but owing to health complaints I had to slow down my work pace’. Response categories are (almost) never, sometimes, often, (almost) always. Psychological well-being of employees will be obtained with the distress screener of the Four-Dimensional Symptom Questionnaire (4DSQ) of Terluin et al. [22], the UWES-9 [23], and the ‘need for recovery’ scale [24]. In addition, return-to-work self-efficacy of employees will be measured with the RTWSE-19 [25].

#### Sick leave

Sick leave frequency and duration (in calendar days) of employees per supervisor, from six months before baseline up to twelve months follow-up, will be measured with both self-reported and objective data. At all measurements, employees will be asked to report sick leave frequency and duration(s) within the last six months. Sick leave data will also be derived from databases of HR and contracted occupational health services.

#### Prognostic measures & possible confounders

At baseline and after twelve months, individual work-related factors of supervisors and employees such as department, job type, and working hours per week will be measured. Additionally, one single item, namely, ‘I am satisfied with my job’, will be used to assess job satisfaction of supervisors and employees. Response categories are never, rarely, sometimes, often, and always. General health of supervisors and employees will be assessed with one item of the SF-36 [26], namely, ‘In general, would you say your health is: excellent, very good, good, fair, or poor?’ Furthermore, three subscales of the Job Content Questionnaire (JCQ) will be used to assess decision authority, supervisor support, and job insecurity of employees [27]. Experienced leadership style by employees will be measured with the Global Transformational Leadership scale (GTL) [28]. At baseline, individual factors such as age, gender, and level of education of supervisors and employees will be obtained. Supervisors will also be asked if they are familiar with PA and if they already apply PA.

### Process evaluation

The framework of Linnan and Steckler will be used to evaluate the implementation process of the PA within the three organisations [29]. The components reach, dose delivered, dose received, fidelity, and recruitment will be assessed after six and twelve months. Data for the process evaluation will be gathered from supervisors and employees using questionnaires and via semi-structured interviews. In a follow-up meeting, representatives of the working group will be asked about barriers and facilitators for the implementation of the PA within their organisation.

### Sample size

The sample size calculation is based on a 10% hypothesized increase in self-efficacy of supervisors in joint problem solving to improve work functioning of employees with health complaints, as a result of the multifaceted implementation strategy of the PA. An intra-class correlation coefficient (ICC) of 0.05 is used to adjust for the cluster randomised design at department level. By using the ICC, the calculation formula for a 10% increase in self-efficacy with the mean score of 6.02 and a SD of 0.88 of the competence scale of Spreitzer et al. leads to a total sample size of 107 supervisors [20], assuming a dropout rate of 20% and taking into account a power (1-beta) of 0.80 and an alpha of 0.05.

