### Randomisation, stratification and blinding

Randomisation will be performed at department level to limit contamination between supervisors of the intervention and control groups. Departments within organisations will be matched as pairs, based on the number of participating supervisors and sick leave frequencies of departments. Randomisation of departments of each pair will be performed by an independent researcher. Inherent in the multifaceted implementation strategy of the PA, it is impossible to blind researchers, supervisors, managers, HR professionals, and OHPs.

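### The stated power of 0.80 for 107 supervisors falls to about 0.74–0.78 once the limited number of randomised departments implied by that figure is counted

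*Protocol article*

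**What the plan says.** The Sample size section of the protocol article works from "the calculation formula for a 10% increase in self-efficacy with the mean score of 6.02 and a SD of 0.88", with "assuming a dropout rate of 20" percent, and "a power (1-beta) of 0.80 and an alpha of 0.05". On clustering it says: "An intra-class correlation coefficient (ICC) of 0.05 is used to adjust for the cluster randomised design at department level". The result "leads to a total sample size of 107 supervisors".

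The section gives no number of supervisors per department, design effect or number of departments, and no other section supplies them.

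Under Randomisation, stratification and blinding, the department is the unit of randomisation: "Departments within organisations will be matched as pairs, based on the number of participating supervisors and sick leave frequencies of departments". It adds: "Randomisation of departments of each pair will be performed by an independent researcher".

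The Statistical analyses section compares changes from baseline between groups with linear mixed models. It provides for adjustment for baseline differences only if randomisation proves unsuccessful, and it names no pair-level analysis.

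**The concern.** An ICC changes a sample size only through the cluster size that it multiplies. The printed inputs therefore do not lead to 107 by themselves, but 107 can be worked backwards to the cluster size it needs, and so to the approximate number of departments. That number is small. A comparison of randomised departments has to estimate between-department variation from those few units, so its reference distribution is a t with few degrees of freedom. The calculation behind 107 appears to use the normal quantiles instead, which overstates power.

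Two things are at stake. The published power for the primary outcome is somewhat too high. Also, a target counted only in supervisors does not protect power, because power depends on how many departments those supervisors come from.

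**Working it through.** **Inputs from the Sample size section.** Difference 10% of 6.02 = 0.602; SD 0.88; ICC 0.05; dropout 20%; power 0.80; alpha 0.05. Two-sided testing and 1:1 allocation are assumed; the section does not state sidedness.

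**Step 1: reproduce 107.**
- Per arm without clustering: 2 × (1.96 + 0.8416)² × (0.88/0.602)² = 33.54, so 34 per arm and 68 in total.
- Dropout only: 68/0.8 = 85. The rest of the way to 107 must come from the design effect, DEFF = 1 + (m − 1) × 0.05, where m is supervisors per department.
- Dividing by 0.8: m = 5 gives 68 × 1.20/0.8 = 102; m = 6 gives 68 × 1.25/0.8 = 106.25, so 107; m = 7 gives 68 × 1.30/0.8 = 110.5, so 111.
- Multiplying by 1.2 for dropout: m = 7 gives 68 × 1.30 × 1.2 = 106.08, so 107.

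So 107 is reproduced at m = 6 or m = 7, depending on how dropout was handled. The number of departments is then 107/6 = 17.8 or 107/7 = 15.3. Departments come in pairs, so this means about 14 to 18.

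**Step 2: power with a cluster-level reference.** With 20% dropout, 0.8 × 107 = 85.6 supervisors are analysed. For k departments of equal size:
- m after dropout = 85.6/k, and DEFF = 1 + 0.05 × (85.6/k − 1)
- SE = 0.88 × √(4 × DEFF/85.6)
- power from the noncentral t with noncentrality 0.602/SE and df = k − 2 (unpaired) or k/2 − 1 (paired)

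For k = 18: m = 4.76, DEFF = 1.188, SE = 0.207, noncentrality 2.90. The two-sided critical value is 2.12 on 16 df, and power is 0.78.

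| Departments | DEFF | Noncentrality | Power, normal | Power, t unpaired | Power, t paired (floor) |
|---|---|---|---|---|---|
| 12 | 1.307 | 2.77 | 0.79 | 0.70 | 0.60 |
| 14 | 1.256 | 2.82 | 0.81 | 0.74 | 0.66 |
| 16 | 1.218 | 2.87 | 0.82 | 0.76 | 0.69 |
| 18 | 1.188 | 2.90 | 0.83 | 0.78 | 0.72 |
| 24 | 1.128 | 2.98 | 0.85 | 0.81 | 0.77 |
| 30 | 1.093 | 3.03 | 0.86 | 0.83 | 0.80 |

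The paired column uses the same SE as the unpaired one and changes only the degrees of freedom. It therefore assumes that matching removes no between-department variance, which makes it a floor.

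**Step 3: other routes to 107.**
- Starting from 35 per arm (a t-based individual calculation) gives m of about 5.5, about 20 departments and unpaired power of 0.77–0.79.
- A one-sided alpha of 0.05 gives m of about 12.7, about 8 departments and unpaired power of 0.72–0.75.

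Each route tried that reproduces 107 ends below 0.80, so the result does not depend on one choice of m. Unequal department sizes would lower the figures further.

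**The case against.** **The cluster size may simply not be printed.** This is a condensed article. Since 107 exceeds 85, some cluster size was evidently used, and the full protocol may state it. That stands: the omission by itself is no error, and 107 is consistent with its inputs. A reader might infer that the arithmetic is wrong; the document does not support that. The point is the power attached to 107.

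**The number of departments is inferred.** Also true. The planned number is not printed, so no single power figure can be called the trial's true power. What holds is a range over the department counts that reproduce 107.

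**Pairing may help.** A reader might take the paired column as the power of this trial. The document does not support that, because it specifies no pair-level analysis and matching is meant to remove variance. If matching removed all between-department variance at 18 departments, the variance factor would fall from 1.188 to 0.95. Noncentrality would then be 0.602/(0.88 × √(4 × 0.95/85.6)) = 3.25, and power on 8 df about 0.81.

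**Baseline data may help.** At 18 departments unpaired, if covariate adjustment multiplies the variance by 1 − r², a baseline correlation of about 0.24 is enough to regain 0.80. Raw change scores multiply it by 2(1 − r), which exceeds 1 when r is below 0.5; at r = 0.4 the noncentrality is 2.90/√1.2 = 2.65 and power about 0.70. The article gives no correlation and the calculation uses none, so the net direction for the final analysis is open.

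**Very few departments.** A reader might infer that the trial could run with, say, 8 departments and power under 0.60. Nothing in the article suggests so few. The Study population section describes about 1,400 supervisors across three organisations.

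**Conclusion.** The concern holds in a limited form. On the stated inputs, the 107 supervisors deliver unpaired power of about 0.74–0.78, not 0.80, at the 14 to 18 departments that the figure implies. That is a shortfall of about 2 to 6 percentage points. It comes from using normal quantiles where a few randomised departments call for a t reference.

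The range assumes a two-sided test, equal department sizes, the printed ICC of 0.05, 20% dropout spread evenly over departments, and no baseline adjustment. Keeping the pairs gives at least 0.72 at 18 departments, and more to the extent that matching works.

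A second consequence is that a target in supervisors alone does not fix the power: 107 supervisors in 12 departments give about 0.70, and in 24 about 0.81.

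The documents do not support the stronger conclusion that the trial as finally analysed must fall short of 0.80. The planned number of departments and any gain from baseline data or matching are not given.

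**What to change.** - State the assumed supervisors per department and the planned number of departments and pairs.
- Restate the power with a cluster-level t reference for the analysis actually planned. On the present inputs this is about 0.74–0.78 unpaired; if pairs are kept, say how much variance matching is assumed to remove.
- If baseline adjustment is relied on to recover power, state the assumed baseline correlation and fix that adjustment in advance.
- Express the recruitment target in departments as well as supervisors. Where feasible, spreading the same 107 over about 24 departments (107/24 = 4.5 each) gives about 0.81 unpaired. About 30 departments are needed for 0.80 if pairs are kept with no matching gain.

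The cost is a slightly less favourable printed power and possibly more, smaller departments to organise. Spreading the same supervisors more widely adds none to the total, but the article does not show whether enough departments of that size can be recruited.

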### Data collection procedure

Data for outcome and prognostic measures, as well as possible confounders, will be gathered using online questionnaires for supervisors and their employees. For those who do not have regular computer access, a paper version of the questionnaire will be sent via postal mail.

### Statistical analyses

Outcome measures will be compared between both groups at baseline, six, and twelve months follow-up. Primary analyses will be performed at supervisor level and secondary analyses at supervisor and employee level. To assess the success of randomisation, descriptive statistics will be used comparing the baseline measurements of the two groups. In case of unsuccessful randomisation, there will be adjustments for baseline differences. The primary independent variable in the analyses will be binominal representing the allocation to either the intervention or control group. The primary dependent variable is self-efficacy of supervisors in joint problem solving to improve work functioning of employees with health complaints. Changes in primary and secondary outcome variables between baseline and follow-up measurements will be compared between the two groups using linear mixed models at supervisor and employee level. All statistical analyses will be performed according to the intention-to-treat principle and, in case of compliance differences of supervisors, per protocol analyses will be performed as well.

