### Study design

This study is a cluster-randomised controlled trial (RCT) in which two implementation strategies will be compared. The PA will be implemented within three organisations: a steel factory, a university medical centre, and a university. Departments of these organisations will be allocated to either the intervention or control group. Intervention departments will receive the multifaceted strategy of the PA and control departments the minimal implementation strategy of the PA. Measurements will take place at baseline and after six and twelve months follow-up. The study protocol has been approved by the Medical Ethics Committee of the VU University Medical Center, Amsterdam, the Netherlands.

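### Baseline adjustment depends on an undefined judgement that randomisation was unsuccessful, and the mixed model's handling of baseline is left open; the cost is pre-specification and power, not average bias

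*Protocol article*

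**What the plan says.** All the relevant text is in the Statistical analyses section of the protocol article.

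- How balance is judged: "To assess the success of randomisation, descriptive statistics will be used comparing the baseline measurements of the two groups". No threshold is given.
- What follows from that judgement: "In case of unsuccessful randomisation, there will be adjustments for baseline differences". The covariates are not named.
- How the groups are compared: "Changes in primary and secondary outcome variables between baseline and follow-up measurements will be compared between the two groups using linear mixed models". This applies to supervisors and employees alike.
- What is modelled: "The primary dependent variable is self-efficacy of supervisors in joint problem solving to improve work functioning of employees with health complaints". This names the score, not its change.

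The Study design section sets the time points: "Measurements will take place at baseline and after six and twelve months follow-up". Under Randomisation, stratification and blinding, departments are paired on number of participating supervisors and on sick leave frequency, an independent researcher randomises within pairs, and the researchers cannot be blinded. Nothing elsewhere in the article makes baseline adjustment unconditional.

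**The concern.** Whether to adjust the primary estimate is decided by looking at baseline data, against no stated criterion, by people who know the allocation. A baseline difference produced by the random allocation is chance. It does not show that randomisation failed, so the trigger does not measure what its wording suggests. Two analysts following the text could report different primary estimates.

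When the trigger is not pulled, the text points to a comparison of changes. If baseline is simply subtracted, that analysis uses the baseline score less efficiently than adjustment does, and its result moves with any chance gap between the arms. The matching gives no direct protection, because departments are not matched on self-efficacy. The baseline score is collected in any case, so adjusting for it every time needs no further data.

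**Working it through.** **Inputs from the Sample size section:** "10% increase in self-efficacy with the mean score of 6.02 and a SD of 0.88"; "taking into account a power (1-beta) of 0.80 and an alpha of 0.05"; ICC 0.05; dropout 20%; total 107 supervisors.

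**Assumptions, not in the article:** two-sided alpha; equal arms; 6 supervisors per department; rho of 0.3, 0.5 or 0.7; the same design effect for every analysis; one follow-up time.

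**1. The plan's own figure.**
- Effect: 0.10 × 6.02 = 0.602 points.
- Per arm: 2 × [0.88 × (1.960 + 0.842) / 0.602]² = 33.5, rounded up to 34, so 68 in total.
- Design effect with 6 per department: 1 + 5 × 0.05 = 1.25, and 68 × 1.25 = 85.
- Dropout: 85 / 0.80 = 106.25, rounded up to 107.

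The figure is reproduced. The cluster size of 6 is back-solved. A size of 7 with dropout added as a multiplier of 1.20 also gives 107 (68 × 1.30 × 1.20 = 106.1). Analysed: 107 × 0.80 = 85.6. The SD of 0.88 belongs to a score, not to a change, so the calculation takes no credit for baseline correlation.

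**2. Size of a chance baseline gap.** SE = 0.88 × √(4 × 1.25 / 107) = 0.190 points. On a normal reference, the absolute gap exceeds 0.2 points in 29% of trials and 0.3 points in about 11%.

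**3. What a gap does to an unadjusted change comparison.** Given a gap b, the expected follow-up difference is the true effect plus rho × b. Subtracting b leaves a shift of -(1-rho) × b. For a gap of one SE the size of the shift is:
- rho 0.3: 0.7 × 0.190 = 0.133 (22% of 0.602)
- rho 0.5: 0.5 × 0.190 = 0.095 (16%)
- rho 0.7: 0.3 × 0.190 = 0.057 (9.5%)

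Over repeated randomisations b averages zero. A simulation with clustered data gave a mean estimate of about 0.60 for a true 0.602 under the change, follow-up-only and baseline-adjusted analyses alike.

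**4. Precision.** In units of SD², the variance factor v is 2(1-rho) for change and 1-rho² with adjustment. SE = 0.88 × √(v × 4 × 1.25 / 85.6) = 0.2127 × √v. Power = Φ(0.602 / SE - 1.960).

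| rho | v, change | v, adjusted | SE, change | SE, adjusted | Power, change | Power, adjusted |
|---|---|---|---|---|---|---|
| 0.3 | 1.40 | 0.91 | 0.252 | 0.203 | 0.67 | 0.84 |
| 0.5 | 1.00 | 0.75 | 0.213 | 0.184 | 0.81 | 0.90 |
| 0.7 | 0.60 | 0.51 | 0.165 | 0.152 | 0.95 | 0.98 |

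The variance ratio is 2(1-rho) / (1-rho²) = 2 / (1+rho), which is above 1 for every rho below 1. At rho 0.8 the SE is only √(0.40 / 0.36) = 1.05 times as large. Below rho 0.5 the change factor exceeds 1, so the change analysis is then less precise than the follow-up score alone.

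**5. The rule as written, with the trigger operating.** The table assumes that adjustment never happens. To see the rule at work, 40,000 trials per setting were simulated with 34 independent subjects per arm (clustering enters only through this effective size), adjusting when the absolute gap exceeded 0.2, 0.3 or 0.42 points. These thresholds are assumed.

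| rho | Power, conditional rule | Power, always adjusted |
|---|---|---|
| 0.3 | 0.66–0.73 | 0.82 |
| 0.5 | 0.80–0.84 | 0.89 |
| 0.7 | 0.95–0.96 | 0.97 |

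The mean estimate was 0.60 throughout. The type I error was 0.031 to 0.046.

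**The case against.** The defence has four parts.

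**The model form is open.** The section names self-efficacy itself as dependent variable, and a mixed model with a common baseline mean also compares changes between groups. The text therefore permits an efficient analysis, and detail of this kind may sit in an analysis plan that is not shown. This stands, and it rules out the claim that the outcome is definitely a change score. It does not rescue the conditional sentence, which is stated outright and implies no adjustment when balance looks acceptable.

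**There is no systematic bias.** A reader might infer that regression to the mean distorts the primary result. It does not on average; the shift is conditional on a chance gap. A reader might also infer that choosing the model from the data inflates false positives. In the simulated rules it did not, and the test was slightly conservative. Both parts of this defence stand.

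**Large gaps would probably be caught.** At rho 0.5 a 0.3-point gap would move the estimate by 0.15, or 25% of 0.602. Such a gap is exceeded in only about 11% of trials, and the rule might well adjust for it. That figure is therefore not the expected error. Still, without a threshold nobody can say which gaps would be caught, and moderate ones would remain.

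**The size rests on unstated quantities.** Neither rho nor cluster size is given, differencing may remove part of a persistent department effect, and two follow-ups are planned. This stands, so only a range can be given.

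**Conclusion.** The point holds as a weakness in pre-specification and efficiency. The article fixes a data-dependent adjustment rule without a criterion and leaves the role of baseline in the mixed model open.

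Read as an unadjusted comparison of changes, the analysis gives up about 17, 10 or 2 percentage points of power at rho 0.3, 0.5 or 0.7 (from the unrounded powers). These are upper bounds under the stated assumptions, since the trigger would adjust in some trials. Planned power of 0.80 is missed only when rho is below about 0.5, and at rho of 0.8 or more the loss is small.

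The documents do not support a stronger conclusion that the primary estimate is biased or the test invalid. This should be fixed because the fix is free, not because the trial would otherwise fail.

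**What to change.** Delete the sentence that makes adjustment conditional. In its place, state in advance that the linear mixed model for every outcome measured at baseline always includes the baseline score, either as a covariate or through a baseline mean common to both arms, whatever balance is observed. Say which of the two forms will be used. The descriptive baseline comparison can stay as a description of the sample, with no bearing on the choice of model.

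The cost is one or two sentences in the Statistical analyses section. No new data and no change in sample size are needed.
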